# Blended cognitive behaviour therapy for children and adolescents with mitochondrial disease targeting fatigue (PowerMe): study protocol for a multiple baseline single case experiment

**DOI:** 10.1186/s13063-021-05126-7

**Published:** 2021-03-01

**Keywords:** Mitochondrial disease, Fatigue, Blended cognitive behaviour therapy, Single case experiment, Children and adolescents

## Abstract

**Background:**

Mitochondrial disease is a rare, hereditary disease with a heterogeneous clinical presentation. However, fatigue is a common and burdensome complaint in children and adolescents with mitochondrial disease. No psychological intervention targeting fatigue exists for paediatric patients with a mitochondrial disease. We designed the PowerMe intervention, a blended cognitive behaviour therapy targeting fatigue in children and adolescents with mitochondrial disease. The aim of the intervention is to reduce perceived fatigue by targeting fatigue-related cognitions and behaviours.

**Methods:**

A multiple baseline single case experiment will be conducted in five children (8–12 years old) and 5 adolescents (12–18 years old) with mitochondrial disease and severe fatigue. Patients will be included in the study for 33 weeks, answering weekly questions about the fatigue. Patients will be randomly assigned a baseline period of 5 to 9 weeks before starting the PowerMe intervention. The intervention consists of face-to-face and online sessions with a therapist and a website with information and assignments. The treatment will be tailored to the individual. Each patient will work on their personalized treatment plan focusing on personally relevant goals. The primary outcome is perceived fatigue. Secondary outcomes are quality of life, school presence and physical functioning.

**Discussion:**

The results of the PowerMe study will provide information on the efficacy of a blended cognitive behaviour therapy on reducing perceived fatigue and its impact on daily life in children and adolescents with mitochondrial disease. Strengths and limitations of the study design are discussed.

**Trial registration:**

Dutch Trial Register NTR 7675. Registered on 17 December 2018. Identifier https://www.trialregister.nl/trial/7433

## Background

Mitochondrial diseases (MD) are rare inherited metabolic diseases; the vast majority are caused by defects in the oxidative phosphorylation system, the final biochemical pathway involved in cellular energy production [1]. Cells that make up organs and tissues that require a lot of energy to function properly contain a higher number of mitochondria. These high-energy organs and tissues are also most commonly affected in a MD; examples are the brain, heart, skeletal muscles and kidneys [2]. As a rule of thumb, symptoms can occur in ‘any organ or tissue, at any age and with any mode of inheritance’ [3, 4]. The severity of the symptoms can vary from mild to highly debilitating complaints. Symptoms can fluctuate over time; they can remain stable over long periods of time, or rapidly deteriorate. The course of the disease is often progressive [5].

Current treatments focus mainly on support and symptomatic relief. Most commonly used interventions include exercise and dietary supplements [5–8]. Psychological interventions may be a valuable addition to improve coping with the symptoms and reduce the impact of the disease in daily life. Psychological interventions have shown to improve symptom load, disability and school attendance in children and adolescents with various somatic complaints (e.g. functional abdominal symptoms, mixed-pain complaints, chronic fatigue syndrome) [9].

Many patients are confronted with the disease and its symptoms during childhood: in 81% of patients diagnosed with MD, onset is before the age of 18 years [10]. Fatigue is often present in children with MD and rated as one of the most burdensome complaints. Perceived fatigue can be defined as an overwhelming sense of tiredness, lack of energy and feeling of exhaustion [11]. Fatigue in patients with chronic diseases, including MD, may be influenced by certain disease-related and generic factors. Disease-related factors that contribute or cause fatigue in patients with MD are directly related to the disease, and could include the mitochondria, and affected organs and tissues [12]. Several generic factors can influence fatigue through cognitions and behaviours [13, 14]. In children with MD, studies show deregulated levels of physical activity, disease-related distress and sleep disturbances [15–19]. In addition, dysfunctional cognitions and behaviours may also be present, such as all-or-nothing behaviour, fear avoidance, symptom focusing and catastrophizing [20]. Cognitions and behaviours can be targeted successfully to reduce fatigue in several chronic diseases by using cognitive behaviour therapy (CBT) [14, 21, 22].

Many generic factors contributing to fatigue can be successfully treated with CBT. The basic components of CBT focus on the relationship between thoughts, feelings and behaviours. To our knowledge, there is no existing psychological intervention targeting severe fatigue in children and adolescents with MD. We propose a blended CBT aimed at reducing perceived fatigue: the PowerMe intervention (see Fig. 1). The intervention is based on existing theories of perpetuating factors in disease-related fatigue [13, 23]. CBT can help patients cope with the many uncertainties and limitations they experience, provide insight and tools to use their energy more optimally and explore barriers and solutions for changing their activities. Online CBT interventions seem to be effective in treating both psychiatric and somatic conditions in children and adolescents [24].

**Fig. 1 Fig1:**
[figure not shown]
Proposed explanatory model of contributing factors to MD-related fatigue and targets of the PowerMe intervention

PowerMe is a combination of face-to-face CBT and an online environment to support therapeutic contact and assignments. Using a mostly online approach will limit travelling for the patients. As a result, patients can more optimally use their time and energy on the intervention [13, 23]. The PowerMe intervention is tailored to the individual patient. Each patient will work on personally relevant goals. In addition, the intervention takes into account the age-related differences in children and adolescents, the diverse clinical phenotype of MD that may cause a variety of consequences in daily life and the presence of (one or more) generic factors contributing to fatigue. All generic factors presented in Fig. 1 can be targeted in the intervention. In addition, parents will be included as an at-home coach to improve the effectiveness of the intervention [25, 26].

Although CBTs are traditionally tested using randomized controlled trials, this study design is not applicable when large groups are difficult or impossible to obtain. A study design focusing on the individual level can also be valuable. Both types of study designs provide important, useful and unique information about the effectiveness of an intervention [27]. To investigate the effect of a tailored intervention in patients with a rare disease, a within-subject design is more feasible. A multiple baseline single case experimental design is suitable, because each participant will act as his or her own control comparing data of the baseline phase with the intervention phase [27–29].

We will investigate the efficacy of the PowerMe intervention in a multiple baseline single case experiment. We hypothesize that the intervention significantly reduces perceived fatigue in severely fatigued children and adolescents with MD. Furthermore, it is hypothesized that due to the character of the intervention, a delayed effect will take place, approximately on the half-way point of the individual treatment (in most cases after 8 weeks). In addition, the efficacy of the PowerMe intervention on reducing the negative impact on daily life will be studied by measuring quality of life, school presence and physical functioning.

## Methods/design

### Study design

A multiple baseline single case experiment will be conducted to evaluate the efficacy of the PowerMe intervention on reducing perceived fatigue in children and adolescents with MD. In addition, the effect of the intervention on quality of life, school presence and physical functioning will be studied.

### Recruitment and study population

Five patients between 8 and 12 years old and five patients between 12 and 18 years old will be included. Specialized metabolic physicians and nurses working at the Radboud Center for Mitochondrial Medicine at the Radboud university medical center in the Netherlands will recruit children diagnosed with MD. Patients will be informed about the PowerMe study during regular medical follow-up, or by an information letter. Furthermore, advertisements will be placed online by the patient organization International Mito Patients (IMP) and the Dutch Foundation for Muscular Diseases (‘Prinses Beatrix Spierfonds’). All interested patients will be screened for eligibility with online questionnaires. Inclusion and exclusion criteria are shown in Table 1. Patients and their parents will sign informed consent forms before filling out the questionnaires. Patients who meet the criteria for a possible anxiety or depressive disorder will be interviewed by a psychologist to make an appropriate assessment of the eligibility of the patient for the study or whether a referral to regular care is advised. Subsequently, the researcher will contact the patient and parents with the results of the screening. If the patient is eligible for the study, the researcher will give a more detailed explanation about the study and answers all questions of the family. Informed consent will then be signed.

**Table 1 Tab1:** Inclusion and exclusion criteria

Inclusion criteria	Exclusion criteria
- Age between 8 and 18 years - Able to speak, write, and read Dutch - Diagnosed with mitochondrial disease (genetically confirmed) - Being severely fatigued (CIS fatigue severity ≥35) - Access to a computer with internet connection - Basic computer skills - Able to travel to the hospital for the CBT intervention (3 sessions)	- Intellectual disability (developmental age younger than 8 years). - Primary depression (CDI ≥16) or anxiety disorder (SCARED-C ≥ 25) - Current psychological treatment for fatigue

### Procedure

To ensure sufficient data points are present to analyse the data, this multiple baseline single case experiment consists of 33 weekly measures of fatigue dispersed over three consecutive phases: baseline, treatment and follow-up. The intervention will be introduced staggered across time. In other words, each participant will start after a different length of the baseline period. The participants are allocated to an intervention start point at random. The following five start points will be randomized: the therapy will start following a baseline period of 5, 6, 7, 8 or 9 weeks. This approach is similar in both groups. The baseline period should be stable. Five to nine data points should give a clear indication of the stability of the baseline [28, 30]. However, extending the baseline period when an unstable baseline is present will cancel out the randomization. For a more rigorous method of testing the effect of the intervention, baseline randomization will be applied. Therefore, baseline stability will not be checked before starting the intervention.

The researcher will contact the patient after randomization has allocated a baseline period between 5 and 9 weeks. At the start of the study, a participant number will be assigned to the patient to ensure confidentiality of personal identifiable patient data throughout the entire study. Participants and their parents receive a link to the online questionnaires each week for 33 weeks: the children fill out assessments about their fatigue and parents report on the school presence of their child. At the start of the study, the patient and parents are asked to fill out additional online questionnaires for the baseline assessment (T0).

After 5–9 weeks, the patient will start with the PowerMe treatment. The guideline for the treatment duration is 16 weeks. However, it can range from 12 to 20 weeks, tailored to the needs of each participant. Afterwards, the patient fills out the (online) post-intervention questionnaires (T1) and continues with the weekly questionnaire for 8–12 weeks. In Fig. 2, an overview of the study design is shown.

**Fig. 2 Fig2:**
[figure not shown]
Guideline of the multiple baseline design used in the study. Note: Phase B can range from 12 to 20 weeks. Phase A′ is adapted to phase B to reach a total of 33 weekly measurements

### Randomization

Unbiased assignment of the baseline period through randomization improves the internal validity of a single case experiment; it protects against readiness or eagerness to participate and rules out any bias by the researcher assigning baseline length to a participant [31, 32]. Therefore, participants will be randomly assigned to a baseline period of 5 to 9 weeks by an independent researcher [29]. Randomization of the starting point of the treatment yields statistical control over known and unknown confounding variables. In addition, the statistical conclusion validity will be enhanced by randomization [31, 33, 34]. In the proposed study, the intervention start point will be determined on a random basis using the Single-Case Data Analysis (SCDA) plug-in package for R software [35].

### Intervention

#### Development

The study and intervention were developed in collaboration with the patient organization IMP. The PowerMe website is built and designed as a healthspace in the webportal of Karify (an ehealth platform based in Utrecht, the Netherlands). The treatment protocol and modules are based on proven CBT protocols focusing on coping with fatigue and chronic illness [13, 23, 36]. Furthermore, a focus group was organized with patients, a board member of the patient organization IMP and a diverse group of health care professionals working with patients with MD. Patients’ needs and wishes for the treatment and website were mapped out and used as a guideline during the development of the blended CBT. In the focus group, patients were asked to reflect on the content, design, lay-out and feasibility of the intervention and the study. Based on their comments, certain topics were added to the intervention as (additional) content in submodules or as information in the library of the website. Furthermore, suggestions for lay-out and design were incorporated as well.

#### The treatment protocol

Trained and experienced CBT therapists and researchers collaborated to write the treatment protocol and the content of the website. The website will be used as a supportive tool within the treatment and contains information, assignments and applications for sending e-mails and making video calls in a secure environment. The website consists of six child modules and one parental module (see Table 2). The modules have been adapted to each age group: children aged 8–12 years and adolescents between 12 and 18 years old. Parents also have their own version of the website, containing all child modules and an additional parental module.

**Table 2 Tab2:** The treatment modules of the PowerMe intervention

Module	Type of module	Content
‘What does your day look like?’	Obligatory	Assignments to guide the treatment plan: Two diaries will be filled out: an activity diary and a sleep diary. The patient will record all activities and rate the fatigue after the activity and enjoyment of the activity. Periods of rest will also be recorded. The sleep diary records among others bedtimes, hours of sleep and quality of the sleep. Both diaries will be filled out for 1–2 weeks. Furthermore, the patient can already write down ideas for possible treatment goals.
‘Knowledge’	Obligatory	The patient will learn more about MD, fatigue related to MD and the PowerMe intervention. It is important that the patient learns information about MD and fatigue that is reliable. Unrealistic ideas about their disease or fatigue can promote unhelpful thoughts and safety behaviours.
‘Thinking, feeling, doing’	Obligatory, including optional assignments	The main focus of this module is the relationship between thoughts, feelings and behaviours in difficult situations, and practicing helpful thoughts. Optional assignments: (1) challenging negative thoughts, (2) identifying cognitive biases and (3) a thought experiment.
‘My battery’	Obligatory, including optional assignments	Information and assignments focused on using their energy more optimally: - Activity diary: Scoring activities and finding ways to change their activities to feel less fatigued (e.g. changing very exhausting activities, different types of rest, balancing between high and low energy activities) - Working on activity-related goals using step-by-step plans - Coping with necessary and/or fun, but exhausting activities - Helping thoughts
‘Sleep’	Optional	Information and assignments about problematic sleep-wake rhythms and sleep hygiene: 1) Making and following a consistent sleep schedule keeping into account: hours of sleep during the night and bedtimes during weekdays and the weekend. 2) Changing problematic sleep hygiene/sleep habits 3) Assignments related to ruminating (thinking helping thoughts, writing down their thoughts, planning 15 min at another time to think things over, relaxation exercises)
‘Me and others’	Optional	Assignments related to communicating about their fatigue and MD. 1) Practice reactions to difficult questions or remarks, either by talking about their disease or reacting assertively. 2) Problem solving, which can focus on a wide range of problems. 3) Communicating their boundaries to help them keep balance between activities and rest.
‘After the treatment’	Obligatory	Together with the therapist, a plan will be made on how to deal with (consequences of) fatigue in the future. Also, the treatment will be evaluated. By writing down the relapse prevention plan within the PowerMe website, all information will be easily found by the patient after the treatment has ended.
‘How can I coach my child?’	Parental module	Parents have the opportunity to coach their child in daily life, whereas the therapist only has weekly contact with the patient. Tips and tricks are provided to help parents support their child during the treatment.

#### Usability testing

The website was tested by three children between 8 and 18 years old, a parent of a child with MD, a young adult with MD, two psychologists and two researchers. Their feedback on readability, usability and layout was used to optimize the final version of the website.

#### The PowerMe intervention

The intervention will be part of an interdisciplinary treatment for patients with MD. Different parts of the treatment must be tested separately before a comprehensive interdisciplinary treatment could be tested. The PowerMe intervention provides tools to help children cope more effectively with their fatigue complaints, and to experience less negative effects of the fatigue in their daily life. The intervention will be tailored by the therapist to the needs of the patient based on the results of the self-report questionnaires, the intake and related assignments. Patients will work on personally relevant goals related to their fatigue. The therapist works closely together with specialized health care professionals to ensure patients work on realistic goals and the therapist can take the possibilities of, for instance, physical activity into account for each patient. Examples of personalized goals are seeing their friends more often, distributing their energy more optimal during the day, accepting their limitations and focusing on possibilities. Additional goals may focus on coping with their disease in general and other consequences of the MD such as pain.

Patients will have three face-to-face sessions and five sessions using video calling, though this may be adapted to the needs and preferences of the patient. The dose is based on other CBT protocols targeting disease-related fatigue or distress [13, 23, 37]. In addition, the therapist will have weekly email or telephone contact with the patient to keep the patient motivated, give feedback on assignments and answer any questions.

The first intake session will be face-to-face with the patient and his/her parents. Afterwards, all patients will start recording their activities and sleep pattern in online diaries (module ‘What does your day look like?’). The second session will focus on setting relevant and realistic goals. Also, the treatment will be more elaborately explained. All participants will then continue with the ‘Knowledge’ module at home. If sleeping problems are considered important contributors to fatigue, the next session will focus on the module ‘Sleep’. This module can also be done as homework. The modules ‘Thinking, feeling, doing’ and ‘My battery’ will be discussed in the following sessions. The start of the module ‘My battery’ will be discussed in a face-to-face session, when possible. After, patients can continue the assignments by themselves or with their parents. An optional module (module 5—‘Me and others’) is given only when the child has a goal related to communication with others. The last module (‘After the treatment’) will be done in the final face-to-face session with the therapist.

Parents will also have an important role in the treatment of their child. They will coach and help their child with the treatment at home. Therefore, parents will receive information on how to coach their child and an overview of all child-modules. Parents of children between the age of 8 and 12 will most likely be present during all sessions. The therapist calls the parents at least once to discuss any questions and give personalized tips on coaching their child. If high levels of parental stress are present on the PIP or mentioned in the intake, the therapist will address these and will provide tools to help them cope with the situation. When parents require specialized help, they are encouraged to see their general practitioner. Parents can also email the therapist if they have any more questions.

### Training, supervision and treatment integrity

The intervention will be given by two healthcare psychologists licensed to treat patients with CBT and experienced in working with children with a chronic disease. The therapists will be trained by a clinical psychologist in using the PowerMe protocol and website. They will receive weekly supervision from an experienced clinical psychologist.

Treatment integrity will be evaluated by recording all sessions and other contact moments with the participant. Sessions and telephone contact will be recorded with permission of the patient and all email-contact will be saved. Treatment fidelity will be measured at the end of the study, by randomly selecting and evaluating therapist adherence to the protocol in 5% of all sessions and phone/email contacts, including the order of the sessions and content within the sessions.

### Refusal of study participation and drop-out

If patients do not wish to participate, they have the option to provide a reason. Both refusals and reasons for refusal will be recorded by the researcher. Drop-outs from the intervention are also recorded. The researcher contacts all drop-outs and records reasons for drop-outs or study-assessments that are not completed. It is not mandatory for participants to provide reasons for dropping-out. When a participant drops-out of the study, another participant will be recruited up to 5 extra participants per group.

### Adverse events

All (serious) adverse events that are reported by the participant or observed by the therapist will be recorded. During the intervention, the therapist will monitor any stress and strain that may arise due to the intervention, or caused by other circumstances, and takes appropriate action. Reported adverse events will be monitored until they have been resolved or a stable situation has been reached. Serious adverse events, as defined by the Dutch law for medical scientific research in humans, will be reported by the researcher to the Research Ethics Committee ‘CMO Region Arnhem-Nijmegen’ that approved the study protocol [38, 39].

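### As written, adverse events in baseline and follow-up (about half of the 33 weeks) depend on unsolicited participant report, so late harm may be under-recorded and any tally by phase would lean towards phase B

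*Protocol article*

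**What the plan says.** The Adverse events section of the protocol article names who may bring an event to the record: "All (serious) adverse events that are reported by the participant or observed by the therapist will be recorded". It sets no time limit on participant reports, and events once reported are followed until they settle. The one monitoring duty it assigns is tied to a phase: "During the intervention, the therapist will monitor any stress and strain that may arise due to the intervention", or from other causes.

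The section on the PowerMe intervention makes the therapist's weekly email or telephone contact part of the treatment. Under Procedure, the study "consists of 33 weekly measures of fatigue dispersed over three consecutive phases: baseline, treatment and follow-up". Of the weekly online link it says that "the children fill out assessments about their fatigue and parents report on the school presence of their child". The Outcomes section adds two weekly impact items for the child and says that parents also give reasons for absence. Table 3 lists no adverse event item at T0, at T1 or weekly.

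**The concern.** There is no control group, and each participant serves as his or her own control. Baseline is therefore the only within-study reference for judging whether an event has to do with treatment. That reference matters here because the Background says of symptoms that "they can remain stable over long periods of time, or rapidly deteriorate", and that the disease often progresses.

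If one phase has a regular observer and the other two rely on a child, possibly as young as 8, to speak up unasked, the chance of an event being recorded changes when treatment starts and again when it ends. A constant background rate could then look like an excess during treatment. A problem that arises after therapist contact ends is less likely to reach the record.

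**Working it through.** **Inputs, all from Procedure and the note to Fig. 2 unless marked**
- Total series T = 33 weeks.
- Baseline A: "the therapy will start following a baseline period of 5, 6, 7, 8 or 9 weeks".
- Treatment B: "The guideline for the treatment duration is 16 weeks", though "it can range from 12 to 20 weeks, tailored to the needs of each participant".
- Follow-up A′ is adjusted so that the total is 33.
- Participants: 5 + 5 = 10 (Recruitment and study population).
- Fraction s of events that unsolicited report captures, relative to the treatment phase: not given; an assumption.

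**Reproducing the plan's own figure.** A′ = 33 − A − B. With B = 16, A = 5 gives 12 and A = 9 gives 8. This matches the 8 to 12 follow-up weeks stated under Procedure. Over B = 12 to 20, A′ runs from 33 − 9 − 20 = 4 to 33 − 5 − 12 = 16.

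**Weeks without a scheduled observer.** This is 33 − B, whatever the baseline length.

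| B (weeks) | 33 − B | Share of 33 | Patient-weeks, 10 participants |
|---|---|---|---|
| 12 | 21 | 63.6% | 210 of 330 |
| 16 | 17 | 51.5% | 170 of 330 |
| 20 | 13 | 39.4% | 130 of 330 |

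**Direction of the bias.** Suppose the true event rate is the same in every phase. The apparent rate ratio of phase B against A and A′ is then 1/s. The share of all events that goes unrecorded at B = 16 is 17(1 − s)/33, taking capture in phase B as complete.

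| Assumed s | Apparent ratio 1/s | Share unrecorded |
|---|---|---|
| 0.25 | 4.0 | 38.6% |
| 0.50 | 2.0 | 25.8% |
| 0.75 | 1.33 | 12.9% |
| 1.00 | 1.0 | 0% |

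This table illustrates direction only. Nothing in the document locates s, and at s = 1 the effect disappears.

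**Other routes in the text.** Weekly fatigue, impact and absence data are collected in all phases, but the Adverse events section does not direct any of them to the adverse event record. The self-rated improvement item can show worsening, but T1 falls straight after treatment and so precedes the follow-up weeks. Drop-outs are contacted by the researcher, but giving a reason is voluntary.

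**The case against.** The strongest reply is that this is a condensed article. Event forms, reporting windows and instructions to families may be in the full protocol. That stands, and it limits the point to the sources and the monitoring period that the article itself states. Missing forms are not part of it.

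Three stronger readings are tempting, and the text does not support them.

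- A reader might infer that late harm is missed. Participant reports have no time limit and reported events are followed up, so the most that can be said is that late harm may be under-recorded.
- A reader might infer that ascertainment switches from nothing to active searching. In phase B the text names only stress and strain and describes no systematic questioning about events. Outside phase B, weekly fatigue, impact and absence reasons can still signal trouble. The contrast is real but softer than that.
- A reader might infer that the trial cannot support its safety conclusions. No comparison of harms between phases is planned: the randomization tests and multilevel models concern the weekly measurements in order to judge fatigue, and other outcomes are described only.

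It is also fair to say that parents have contact with the therapist during treatment and can email. That contact is part of the intervention and does not fill the gap in baseline and follow-up.

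Finally, a weekly health prompt could be reactive. The Background lists symptom focusing and catastrophizing among the cognitions that may be present, and the primary outcome is the child's own fatigue rating. This stands and shapes the fix: ask the parent, not the child.

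**Conclusion.** The point holds as an inexpensive improvement to safety recording. As written, therapist monitoring covers about 16 of 33 weeks (range 12 to 20). The other 17 (range 13 to 21) rest on unsolicited participant report, although parents already answer a form in each of those weeks. Late harm may be under-recorded, and any description of events by phase would be tilted towards phase B. The week counts follow from the document. The direction of the tilt assumes only that unsolicited report captures less than weekly therapist contact does. Its size is unknown, and no inflation factor should be quoted as a finding. The primary fatigue analysis is not affected.

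**What to change.** - Add one fixed item to the parents' existing weekly online form in all 33 weeks: any new or worsened health problem, unplanned medical contact or admission since the last form. Ask the parent only, to limit reactivity with the child's self-reported fatigue.
- In the Adverse events section, name parents and the weekly absence reasons as sources.
- Have the researcher log the answers each week.
- Describe events per patient-week by phase from this uniform source, and list therapist-observed events separately. Coverage by a scheduled question becomes 33 of 33 weeks, or 330 patient-weeks for ten participants. Scheduled therapist contact now covers 160 (range 120 to 200).

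The cost is one questionnaire item, a few minutes of researcher time per week and a small amendment, with no extra visits or staff. Parents carry slightly more burden and more non-serious events will be recorded. Under Trial status, recruitment was still running and was expected to end in February 2021. If the item is added mid-trial, earlier participants will lack it and their events should be reported separately.
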